# Design and Methods

## Study Design

We propose to conduct a double blind, placebo controlled, randomized controlled efficacy trial (RCT) among children under longitudinal observation to examine the above-mentioned questions. Children will be recruited during the first EPI visit at 6 weeks of age and will be followed prospectively with collection of epidemiologic, clinical, and laboratory data. Routine EPI visits in Kenya occur at 6, 10, and 14 weeks, and again at 9 months of age. IPTi will be provided under supervision at 10 and 14 weeks and again at 9 months with one of 3 drug regimens or placebo. From ages 2-6 months, supplementation with ferrous sulfate will be given as part of the intervention package.

The 4 arms of the study are as follows

I Intermittent SP/AS3 treatment with daily iron supplementation

II Intermittent Lapdap treatment with daily iron supplementation

III Intermittent AQ/AS3 treatment with daily iron supplementation

IV Intermittent placebo treatment with daily iron supplementation

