### Exclusion criteria

1. Known allergy to any of the study drugs

2. Current Cotrimoxazole prophylaxis

3. Concomitant disease requiring hospitalization or transfusion

4. Plans to be away from the study area for more than 6 months during the next year

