## Assignment to interventions

All infants whose parents or guardians agree to participate in the study will be assigned to one of the 4 treatment groups through permuted block randomization[50]. The randomization code will be prepared before the trial starts.

These randomization procedures are expected to minimize the possible influence of geographical location and seasonal malaria variations.

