## Intervention clinic visits

Enrolled infants returning to clinic at 10 weeks will be given study drugs and will be measured for recumbent length, weight, and mid-arm upper arm circumference. Capillary blood samples will be taken using finger or heel prick for later G6PD enzyme level testing. Blood will be collected on filter paper at the 10 week visit for later testing for genetic markers for drug resistance. Infants returning to the clinic at14 weeks will be given the 2nd dose of the study drugs. At the 9-month visit, infants will be given the final dose of the study drugs and a capillary blood sample will be taken for later measles serology testing.

A questionnaire soliciting information about overall health of the baby, febrile episodes, other intercurrent illnesses, use of other medications, ITN usage, and compliance with iron will be administered at each clinic visit. The form will be based on the OPD surveillance form used in the DSS, but will solicit more detailed information. Infants whose caretakers state that their child has been given CTX in the past 2 weeks will either a.) not be given the dose of intervention drug until 2 weeks after CTX was given, or b.) be withdrawn from the study (if CTX is given as a daily dose).

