Any child that has an allergic reaction (severe cutaneous reaction, anaphylaxis, or other severe reaction) associated with any study drug will be withdrawn from receiving further study drug. The study code will be broken for that child, so that a determination of possible drug allergy can be determined. Parents will be informed about the possible allergy, and that information will be recorded on the child health card. If future treatment for malaria is needed, parents will be informed that it should be carried out with a drug other than one in the class to which the child had a reaction. The child will continue to be followed as per protocol with the exception that the child will not receive any additional doses of study medication. The parent or guardian maintains the right to completely withdraw the child from the trial at any time (meaning that no further follow-up would occur).

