**Data Management**

Data cleaning and storage:

Quantitative data will be entered using scan-ready forms and an optical scanner. Data will be entered and edited in Kenya. Images of scan forms will be kept on a secure server with access limited to study personnel. Data analysis will be undertaken collaboratively in Kenya and at CDC in Atlanta. Access to study computers will be restricted to study personnel, and paper records will be secured in locked cabinets in Kenya. Paper records will not be transported to Atlanta. Electronic files will be transferred to Atlanta either as password-protected e-mail attachments or as password protected files on zip disks or CDs.

Sample storage

Specimens will be stored in locked freezers or cabinets with identifiers at KEMRI and at CDC, to which only study personnel will have access.

In accordance with WHO advice, testing for serological responses to EPI antigens will be performed at a single commercial reference laboratory. The commercial laboratory will only have coded specimens, and will not be engaged in the research. Any remaining sera will be shipped back to Kenya.

Statistical analysis:

SAS software (SAS Institute, Cary, NC), and STATA software (STATA corporation, College Station, TX) will be used for quantitative data analysis. The primary analysis will be based on intention to treat. The analysis will be time to first clinical malaria comparing each of the study drug arms to the placebo arm. Mild, moderate, and severe anemia will also be compared between each study drug arm and the placebo arm.

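### Randomised infants found on daily cotrimoxazole are withdrawn from the study rather than only from study drug, which creates avoidable and possibly informative censoring in the intention-to-treat analysis

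*Protocol*

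**What the plan says.** Under Intervention clinic visits, the protocol gives two rules for an infant whose caretaker reports CTX in the preceding two weeks. With recent, non-daily use the infant will "not be given the dose of intervention drug until 2 weeks after CTX was given". With daily use the infant will "be withdrawn from the study (if CTX is given as a daily dose".

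Three other statements fix when this rule acts:

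- Exclusion criteria lists "Current Cotrimoxazole prophylaxis", so the rule is aimed at infants who start CTX after entry.
- Study Design: "Children will be recruited during the first EPI visit at 6 weeks of age".
- Assignment to interventions: "All infants whose parents or guardians agree to participate in the study will be assigned to one of the 4 treatment groups".

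Two statements bear on what should happen to such infants:

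- Data Management, under statistical analysis: "The primary analysis will be based on intention to treat". The analysis is time to first clinical malaria, each drug arm against placebo.
- Unscheduled visits, on a child with an allergic reaction to study drug: "The child will continue to be followed as per protocol with the exception that the child will not receive any additional doses of study medication". That same paragraph treats complete withdrawal, described there as the parent's choice, as the end of follow-up.

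**The concern.** An intention-to-treat comparison depends on following infants for outcomes whatever happens to their treatment. Here the protocol itself ends follow-up because of something that happens after allocation. If the reasons for starting daily CTX are related to an infant's risk of malaria, anemia or admission, the censoring is informative. No later analysis can restore outcomes that were not collected.

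At stake are the primary endpoint and the secondary endpoints of anemia, vaccine serology and all-cause hospitalisation, including the 12-month hemoglobin and serology in the Study Schedule. For infants who have already had a course of study drug, the trial's own safety follow-up also ends early.

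**Working it through.** **Step 1: does the rule act after randomisation?** Recruitment is at 6 weeks and allocation follows parental agreement. The rule is applied at the 10-week, 14-week and 9-month visits, so all three come after allocation. The Iron section speaks of recruitment at 10 weeks. Even on that reading, the 14-week and 9-month visits come after allocation.

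**Step 2: is withdrawal from the study loose wording for stopping study drug?** Comparing the three drug-related situations suggests not:

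| Situation | Study drug | Follow-up |
| --- | --- | --- |
| Recent, non-daily CTX (Intervention clinic visits) | Dose deferred | Continues |
| Allergic reaction (Unscheduled visits) | Stopped | Continues, stated explicitly |
| Daily CTX (Intervention clinic visits) | Ends with withdrawal | Ends with withdrawal; nothing retains the infant |

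Elsewhere, then, the protocol separates stopping drug from ending follow-up. For daily CTX it does not.

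**Step 3: the protocol's own sample size.** Inputs from Sample Size: protective efficacy 40% (hazard ratio 0.6), alpha 0.017, power 90%, placebo median 68 weeks, 250 per arm. Three things are assumed: a two-sided test, exponential times, and 68 weeks of follow-up (the follow-up length at which the stated figure reproduces).

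- Events per pairwise comparison (Schoenfeld): 4 × (2.387 + 1.282)² / (ln 0.6)² = 206.3, so 207.
- Event probabilities at 68 weeks: placebo 0.50; active 1 − 0.5^0.6 = 0.34; mean 0.42.
- Per arm: 207 / (2 × 0.4201) = 246.4, so 247, against 250 stated.
- Attrition: 250 / (1 − 0.11 − 0.10 − 0.13) = 250 / 0.66 = 379, and 4 × 379 = 1516, exactly as stated.

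The three deductions are for the outcome present at baseline, loss to follow-up and mortality. None is specifically for withdrawals that the protocol orders.

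**Step 4: power if such infants are lost.** The protocol gives no rate of daily CTX starts, so 2%, 5% and 10% are assumed (about 30, 76 and 152 of 1516 infants). Each is taken off the 250 per arm. Power = Φ(√(D × (ln 0.6)² / 4) − 2.387), where D = 2 × n per arm × 0.4201.

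| Lost | n per arm | Expected events D | Power |
| --- | --- | --- | --- |
| 0% | 250 | 210.1 | 90.6% |
| 2% | 245 | 205.9 | 89.9% |
| 5% | 237.5 | 199.6 | 88.9% |
| 10% | 225 | 189.1 | 87.0% |

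This counts each withdrawn infant as contributing nothing. It therefore overstates the loss for those withdrawn at 14 weeks or 9 months, who have already contributed time and possibly an event.

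The objectives concern the first year of life. If follow-up were instead cut at about 42 weeks after the 10-week visit, power would start at 75.0% and fall to 69.8% with a 10% loss. The starting point is lower, but the drop is of similar size.

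**The case against.** A reader might infer that the rule breaks the intention-to-treat analysis outright. The protocol does not support that. Nothing removes these infants from the analysis set. In a time-to-first-event analysis they can be counted in their allocated arm, with earlier events included, and censored at withdrawal. How censoring is handled may properly be left to an analysis plan. What stands is that the censoring may be informative, and an analysis plan cannot supply outcomes that were never collected.

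A reader might also infer that all hospital and death outcomes are lost. That is too strong as well. The Demographic Surveillance System section describes monitoring at 7 outpatient and 2 inpatient facilities, with village reporters recording births and deaths, independently of the trial. Mortality is not a listed objective, although all deaths go to the Data Safety and Monitoring Board within a week. But linkage is estimated at about 80%, and no section says these data will be used for withdrawn infants. The surveillance is not described as making the trial's scheduled hemoglobin or serology measurements.

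Finally, the link to illness is an inference, because the protocol does not say why daily CTX would be started. It offers no evidence of a link to arm, and the trial is double-blind. Withdrawal at the 10-week visit comes before any study drug, so study drug cannot have caused it and no safety follow-up of a dosed infant is lost. Those two arguments apply only to withdrawals at 14 weeks and 9 months. The 10% allowance for loss to follow-up may also absorb some of the numbers.

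**Conclusion.** The point holds as a defect in follow-up. The rule stops the trial's own outcome collection in a group of randomised infants defined by an event after allocation. That sits badly with the intention-to-treat primary analysis and is inconsistent with the protocol's handling of allergic reactions.

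The power cost is small: about 1 to 4 percentage points for assumed losses of 2% to 10%, on the 250-per-arm, 68-week basis. The concern is validity. The direction and size of any bias cannot be derived from the protocol, because neither the frequency of daily CTX nor the reasons for it are given. The protocol does not show that these infants are sicker, that withdrawal differs by arm, or that intention to treat is abandoned. It shows that outcomes would go uncollected for no stated reason, and that this has to be corrected in the protocol rather than at analysis.

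**What to change.** Reconcile Intervention clinic visits with Unscheduled visits and with the intention-to-treat statement in Data Management. State that infants found on daily CTX remain in all scheduled follow-up and outcome collection and are analysed in their allocated arm. Record the CTX start date, and use censoring at that date only as a sensitivity analysis. This concerns follow-up and analysis alone: whether study drug is given to an infant on CTX is a clinical matter, and the existing rule on that is left unchanged.

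The cost is about a sentence in the protocol, one recorded date, and visits already planned for every enrolled infant. The statistical downside is a small dilution of the estimated effect, because some of these infants will not have had the full set of courses.

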If the infant is reported or observed to be ill, a full clinical exam will be performed. Infants at the 10- and 14-week visits who have documented fever (> 37.5 C by axillary measurement) or history of recent fever (previous 48 hours) will have an RDT for malaria performed. If the RDT is positive, in order to maintain blinding of the study groups, there will be a treatment regimen paired to each of the study arms. In the case of the three arms that include an antimalarial (SP/AS, AQ/AS and Lapdap), the “treatment” drug will in fact be a placebo. Each of the three non-placebo arms of the study involves the administration of a drug that is adequate and appropriate treatment for malaria. In the case of children enrolled in the placebo arm of the trial, the treatment drug will be a 7-day course of quinine, which is one of the MOH recommended drugs for treatment of malaria. The guardians of all febrile children will also be provided with a 3-day supply of acetaminophen (paracetomol). A blood film will also be performed on all infants who have an RDT performed. Any infant who was febrile, but had a negative RDT and is found to have parasitemia by blood film will be given antimalarial treatment in accordance with the paired scheme above. Infants who appear pale will have their hemoglobin measured. Infants with Hb<8 g/dl at the 9 month visit (as infants at the 10 and 14-week visits will already be taking iron) will receive iron per the national policy.

At each of the study clinics, compliance monitors will work in conjunction with a village recorder to remind enrolled families (with an oral and written message delivered to the home) about upcoming study clinic visits. A compliance monitor will visit the houses of families who fail to appear within one week of an intervention visit (10 weeks, 14 weeks, and 9 months).

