## Follow-up clinic visits (non study drug administration visits)

Parents will be asked to bring enrolled infants back to the clinic for follow up visits at 18 weeks, and at 12, 18, and 24 months. A compliance monitor will visit the houses of families who fail to appear within 2 weeks of a follow-up visit. To facilitate the work of compliance monitors, a photograph of each mother and child will be made at enrolment, and that photograph kept with a map locating the place of residence. These documents will be returned to the mother at the conclusion of the study or destroyed.

At the 18-week visit, blood (from the same finger prick) will be obtained and frozen at –70C for later determination of post-vaccination serologic testing for antibodies to polio, diphtheria, tetanus, hepatitis B, and Hib. At the 12-month visit, blood will be obtained for determination of sickle cell trait and frozen for later determination of measles antibody titer. Blood will also be collected on filter paper for later testing of genetic markers for drug resistance.

A questionnaire (identical to that administered during the intervention visits) soliciting information about overall health of the baby, febrile episodes, other intercurrent illnesses, use of other medications, ITN usage, and compliance with iron will be administered.

The algorithm for antimalarial treatment of children who are febrile at the 18 week, and at 12, 18, and 24 month visits will be the same as for the intervention visits, with the exception that all infants who need treatment will be provided quinine (18-week visit) or Coartem (12, 18, and 24-month visit if the child weighs at least 5 kg), as no children will be receiving study drugs at these visits. Children weighing less than 5 kg requiring antimalarial treatment will receive quinine. Children with severe malaria will treated with quinine, regardless of age. Infants with Hb<8 g/dl at the 12, 18, or 24-month visits will be treated with iron per the national policy.

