## Risk/benefit information

Benefits to participating infants include free health care for routine childhood illnesses (malaria, anemia, diarrhea, and acute upper and lower respiratory infections) for a period of 24 months starting from the first day of that child’s enrollment in the study. The IPTi study ID card will also serve as a “health passport” which allows the child to receive free treatment for these conditions in one of the study health facilities for this period. The child will be seen by a dedicated study clinician, which may result in shorter wait times for medical care. Inpatient hospital costs at Lwak and Abidha hospitals will also be covered for enrolled children. Any other medical costs (e.g. specialty care) are not covered by the project unless the illness is deemed to have been caused by one of the study medications. All children will receive free iron, which has demonstrated benefits in reducing anemia. Not all children will receive routine antimalarials (i.e. the IPTi intervention) because the benefit of IPTi is not known in this setting. Because enrolled children will visit the clinic 5 extra times during the study, they are likely to have malaria and severe anemia detected and treated more quickly than usual. In addition, enrolled children will be receiving RDT and blood film diagnosis for febrile illnesses, which may allow for more accurate diagnosis and appropriate treatment of these illnesses. Guardians will be informed if an enrolled child has sickle cell disease deficiency, which might help to prevent adverse outcomes.

During weekends and evenings, a nurse will be available to assist IPTi participants who are severely ill. The nurse will be stationed at Lwak hospital, our most central study clinic. In cases where the infant must be hospitalized, the nurse will provide stabilizing treatment and the IPTi Field Supervisor, Coordinator, or designee will arrange transport to Bondo or Provincial hospital. This may benefit very ill infants. Guardians of infants who are critically anemic (Hb < 5) will be provided transport to a hospital (Kisumu or Siaya) for evaluation and treatment.

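### The blinded paired treatment at the 10- and 14-week visits has no severity limit, and the protocol's quinine rule for severe malaria is not carried to those visits

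*Protocol*

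**What the plan says.** **Intervention clinic visits.** An infant seen at 10 or 14 weeks with fever, or with a history of fever in the previous 48 hours, has an RDT. If it is positive, "there will be a treatment regimen paired to each of the study arms", for the sake of blinding. In the SP/AS, AQ/AS and Lapdap arms the paired drug is placebo; in the placebo arm it is seven days of quinine. The justification is that "Each of the three non-placebo arms of the study involves the administration of a drug that is adequate and appropriate treatment for malaria". A febrile infant with a negative RDT who is later "found to have parasitemia by blood film will be given antimalarial treatment in accordance with the paired scheme above". The only text bearing on severity is "If the infant is reported or observed to be ill, a full clinical exam will be performed" and a hemoglobin check for infants who look pale.

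**Follow-up clinic visits.** For 18 weeks and 12, 18 and 24 months, the treatment algorithm "will be the same as for the intervention visits", except that quinine or Coartem is given to all who need treatment, "as no children will be receiving study drugs at these visits". The same paragraph adds: "Children with severe malaria will treated with quinine, regardless of age".

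**Unscheduled visits.** A febrile study infant with a positive RDT before the 12-month visit receives quinine, whatever the arm.

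**The concern.** The paired scheme is a sensible way to keep the blind when an infant has mild illness and has just received an effective antimalarial as study drug. Its wording goes further than that. Fever and parasites trigger it, severity plays no part, and the reason given for an inert paired drug covers malaria of any degree.

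Elsewhere the protocol treats severe malaria as a separate case needing quinine. If the scheme is followed as written at these two visits, a severely ill infant gets quinine that day in the placebo arm and not in the other three. Clinic staff do not know which applies to the child in front of them. What is at stake is the care of individual infants. The estimate of efficacy is not in question.

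**Working it through.** No figure in the plan is in dispute, so the check sets the relevant rules side by side for one case: an infant with severe malaria and a positive RDT.

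| Where the infant is seen | Active arms | Placebo arm |
| --- | --- | --- |
| 10- or 14-week visit (Intervention clinic visits) | study drug plus paired placebo | study placebo plus quinine |
| 18 weeks, 12, 18 or 24 months (Follow-up clinic visits) | quinine | quinine |
| Unscheduled, before the 12-month visit (Unscheduled visits) | quinine | quinine |

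Only in the first row does same-day quinine depend on allocation.

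**Can the severe-malaria sentence be read back into the first row?**

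1. It stands under a heading for visits without study drug, directly after the weight rule for Coartem and quinine. In context it most naturally overrides that choice. On this reading the 10- and 14-week visits have no rule for severe malaria.
2. It is worded by disease state and applies at any age, so it can also be read as general. It would then displace the paired placebo for a severe case, but neither section says so or refers to the other.
3. The stated link runs one way. The follow-up algorithm takes over the intervention-visit algorithm with exceptions, and nothing takes the severe-malaria exception back.

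**Does another provision remove a severe case from the scheme?**

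- The exclusion for disease requiring hospitalization or transfusion is an entry criterion and does not address illness arising at 10 or 14 weeks.
- Code-breaking (Unscheduled visits; Risk/benefit information) is tied to allergic or severe adverse reactions, not to severe malaria.
- The full examination of an ill infant helps staff recognise severity, but no step is stated that takes the infant out of the scheme.

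**Does the protocol's own material support the unqualified justification?** The reference list gives reason for a limit. The titles of references 23, 25, 35 and 36, cited for the study regimens, are confined to non-severe or uncomplicated malaria.

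**Scale.** The Sample Size section plans 379 infants per arm. Infants allocated to an arm whose paired drug is placebo: 3 × 379 = 1,137, and 1,137 / 1,516 = 75% of planned enrollment. This is the population under the rule, not the number affected. The protocol gives no rate of severe malaria at 10 to 14 weeks. The background rate of severe malarial anemia (15–60 per 1,000 children under 5 per year) cannot stand in for it, because it counts Hb < 5 cases, which already have a hospital route, over a much wider age range.

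**The case against.** The strongest reply is that the paired scheme is plainly an outpatient scheme. It concerns infants attending scheduled vaccination visits, who may have only a history of fever, and who go home with acetaminophen. Nothing in it forbids quinine or referral, and staff know that the paired drug may be inert.

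Admission is also presupposed in every arm:

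- All-cause hospitalization is a secondary objective.
- Hospitalization for malaria is an anticipated event (Adverse Event Reporting), and admissions from expected causes go to the DSMB quarterly.
- Inpatient costs at Lwak and Abidha are covered, and both names are among the study clinics.
- Guardians of infants with Hb < 5 "will be provided transport to a hospital (Kisumu or Siaya) for evaluation and treatment".
- A nurse covers weekends and evenings and can arrange transfer, and study staff see dosed infants again on days 2 and 3.

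Much of this stands. It makes it likely that a severely ill infant would be referred whatever the arm. It does not supply the missing instruction: none of these provisions says that an infant with severe malaria and Hb of 5 or more leaves the paired scheme on the day.

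A reader might infer a head-on contradiction between the two sections. The text does not support that, because the severe-malaria rule can be confined to the follow-up visits and then does not meet the paired scheme at all. A reader might also infer that the protocol prohibits quinine for severe cases in the active arms. It is silent on them, which is a different fault. It is fair to add that the Definitions section does not define severe malaria, but the existing quinine rule already rests on that undefined term.

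**Conclusion.** The point holds as a gap in a stated clinical rule. The paired scheme and its justification have no severity limit, and the severe-malaria rule is not carried to the 10- and 14-week visits. Read as written, same-day quinine for a severely ill infant there depends on the blinded arm.

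The practical risk is low given the provisions for admission, and the number affected cannot be estimated from the documents. The primary analysis and the sample size are not affected. The conclusion rests on the wording alone. It assumes nothing about the route of quinine or about how the study regimens perform in uncomplicated malaria, and it does not question the paired scheme for such cases. It is a cheap improvement to patient safety.

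**What to change.** Amend Intervention clinic visits as follows:

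1. Limit the paired scheme, and the sentence calling the study drugs sufficient treatment, to uncomplicated malaria.
2. State that in every arm an infant judged clinically, without knowledge of the arm, to have severe malaria at a 10- or 14-week visit receives open-label quinine and hospital referral instead of the paired drug. Apply the same rule on reassessment after a later positive film.
3. State that any study dose not yet given is deferred until recovery. The same section already defers doses after cotrimoxazole.

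The cost is a few sentences and a clinical reassessment step for infants found positive later by film. A few study doses may be deferred or missed; those infants stay in the intention-to-treat analysis. No code need be broken, because severity is judged blind and the same open-label drug is given in every arm. Randomization and drug packs do not change.
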